**Chickenpox**	
Whether the individual has ever been infected with chickenpox, also known as varicella.	This will be measured using the corresponding ICD-10 code **B01**. Because only information between 2013 and 2021 is available and chickenpox usually occur during childhood, most of the actually occurred infections will be missed.
**Vaccination plan**	
For individuals with MS, IBD, or CIRD it is not unusual that the vaccination is planned in advance by the physician and aligned with changes in medication that may have immunosuppressive effects. For example, the physician may decide that the individual should be vaccinated next week. To allow the patients immune system to make a proper response to the vaccination, a new prescription of immunosuppressive medication is then delayed for a few weeks. This variable states whether such a plan was made or not.	An indicator of whether a person receives a medication change shortly after vaccination may be created. However, this type of indicator breaks the time-line, since information from the future would be used. We will perform an additional sensitivity analysis to determine the effect of using this indicator as an adjustment variable.

Using this DAG and the *backdoor criterion* (47), we then identified separate sets of factors that we need to adjust for in each vaccine effectiveness analysis (53). These sufficient adjustment sets are very similar. In both of the two considered analyses, we will adjust for *Age, Sex, Place, Calender Time, Cautiousness, Disease Status, Healthcare-Seeking Behavior* (HSB), *Treatment, Health Status*, and *Vaccination Plan*. The only differences are that we additionally have to adjust for *Chicken Pox* and *Herpes Zoster Immunity* in the herpes zoster vaccine effectiveness analysis and that we also have to adjust for *Influenza Immunity* in the influenza vaccine effectiveness analysis.

Note that, given our assumptions, there is no need to adjust for socioeconomic status in either analysis, because we hypothesize that the effect of this variable on each outcome is only indirect and is thus already adjusted for by including the other variables. It is also not strictly necessary to adjust for sex in the influenza vaccine effectiveness analysis for the same reason. We choose to include sex anyway, because it can be seen as a proxy for other relevant confounders such as cautiousness that we may not be able to fully adjust for given the mentioned indicators (48).

For most of the relevant confounders identified through the DAG, one or multiple indicators can be extracted from the available BARMER data, as described above. However, this is not the case for all confounders. For example, we were unable to identify valid indicators for the *Cautiousness* of an individual. We are thus unable to adjust for all confounders, potentially resulting in a violation of the *conditional exchangeability* assumption (e.g., that the groups are exchangeable given the observed confounders) (32). Although social contact behavior is a crucial factor in infection transmission and thus an important predictor for the outcomes in our study, its role as a predictor for vaccination decisions is less clear. A study by Ibuka et al. (54) indicates that people with less cautious contact behavior only have a slightly higher chance of getting vaccinated. We therefore expect the bias introduced by this unmeasured confounder to not be substantial.

An additional issue in the adjustment is that not all considered confounders are measured perfectly. In particular, the influenza and herpes zoster immunity at baseline will likely be underestimated, because not all individuals who experienced an infection visited a medical professional because of it. Hence, not all infections are included in the data, resulting in some individuals appearing as not having been infected, despite having been infected. Furthermore, because we only have access to the data between 2013 and 2021, we will likely underestimate the true extent of the existing herpes zoster immunity as well, because most chickenpox infections happen during childhood and we did not measure childhood vaccinations. These measurement errors may result in additional residual confounding (43). Sensitivity analysis will be performed to further quantify this potential source of bias, as described in Section 2.6.6.

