**Cautiousness**	
The degree of cautiousness displayed by an individuals social contact patterns and general precautionary social behavior.	Stuurman et al. (48) mention the number of people living in the individuals household and the presence of a child in the individuals household as indicators for this variable. This information is, however, not available in the BARMER database.

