#### 2.6.6 Negative control outcome analysis

To quantify the amount of residual confounding, a negative control outcome analysis will be performed (73). In this strategy, the analysis is repeated with suitable negative control outcomes, which are variables that ideally have the same causes as the actual outcome of interest, but are not directly caused by the exposure of interest. We will use *medically attended urinary tract infection* as a negative control outcome for all considered analyses. In particular, we will use inpatient and outpatient diagnoses (ICD-10 code N39.0) with an associated prescription for a relevant antibiotic to identify the infections (see online supplement). This outcome has been used in other vaccine effectiveness studies for influenza- (73, 74), herpes zoster- (75), and pneumococcal vaccines (76). These studies additionally used other negative control outcomes, such as hip fractures and fractures of the hand or wrist. We choose not to use these outcomes here, due to their potentially large association with corticosteroid medication (77), which we can only partially adjust for in our analysis through the category of received medications. Our strategy to identify the exact dates of outpatient diagnosis is again described in the online supplement.

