## 3 Discussion

The proposed study has multiple strengths. One of the biggest strengths is its large sample size. With approximately 50,000 MS patients, 300,000 CIRD patients, 80,000 IBD patients and potentially millions of control patients, this study is, to the best of our knowledge, the largest of its kind. Because it is based on data from a German health insurance provider, it also contains information on the medications prescribed to each patient, as well as their acquired infections and comorbidities. This large sample size makes a detailed disease specific population based comparison of the vaccine effectiveness with appropriate controls possible. The available information also makes adjustment for many of the relevant confounders feasible. The very limited amount of inclusion criteria additionally facilitates the generalizability of the obtained results.

A limitation of this study is the potential of unmeasured or unknown confounding. As discussed earlier, we are not able to adjust for all confounders that were identified by our assumptions about the causal data generation process. For example, it is impossible to measure social contact behavior from the available data. It is also possible, if not likely, that the DAG we specified is partially wrong or fails to include other, currently unknown, confounders. This is a frequent problem in observational studies, although it is not always acknowledged (32). We will attempt to quantify the impact of this potential source of bias through pre-planned sensitivity analyses.

A further limitation is the potential of misclassification of the vaccination status due to individuals getting vaccinated through their company physicians, or in rarer cases in hospitals or pharmacies. Because some individuals will be misclassified as “unvaccinated,” it is possible that the estimates of the vaccine effectiveness will be biased downwards. However, we expect this to be a minor issue, because most individuals in Germany get vaccinated through their primary care physician. Under the assumption that the misclassification rate does not differ between the considered disease groups, we would also not expect bias of the contrast between the vaccine effectiveness estimates.

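### Section 2.5.4 sends the bias from under-recorded influenza and zoster immunity to Section 2.6.6, but the urinary tract infection control there cannot quantify it

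*Protocol article*

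**What the plan says.** Section 2.5.4 names two gaps in confounder adjustment.

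- **Cautiousness.** It belongs to the adjustment set of both analyses, but "we were unable to identify valid indicators for the *Cautiousness* of an individual". Table 2 defines it as "The degree of cautiousness displayed by an individuals social contact patterns and general precautionary social behavior".
- **Immunity.** The article states that "the influenza and herpes zoster immunity at baseline will likely be underestimated", because infections that never reached a physician are not in the claims. Childhood chickenpox is also largely outside the data window. On the resulting bias it says: "Sensitivity analysis will be performed to further quantify this potential source of bias, as described in Section 2.6.6".

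Section 2.6.6 opens with its purpose: "To quantify the amount of residual confounding, a negative control outcome analysis will be performed". It describes suitable controls as "variables that ideally have the same causes as the actual outcome of interest, but are not directly caused by the exposure of interest", and then names the single control: "We will use *medically attended urinary tract infection* as a negative control outcome for all considered analyses".

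The Discussion (Section 3) turns to unmeasured confounding, with social contact behaviour as its example, and says: "We will attempt to quantify the impact of this potential source of bias through pre-planned sensitivity analyses".

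**The concern.** A negative control outcome shows a confounder's bias only to the extent that the confounder also affects the control outcome. The immunity variables in Table 2 are specific to a pathogen: earlier influenza infection or vaccination, earlier zoster, and chickenpox. Nothing in the text makes any of them a cause of UTI. The cross-reference in Section 2.5.4 therefore credits Section 2.6.6 with a property it does not have.

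The estimates at stake are the VE in each group and the primary contrast, which Table 1 defines as the ratio of VE between diseased and non-diseased persons. If unrecorded immunity is balanced differently across disease groups, the ratio can shift while the control shows nothing.

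**Working it through.** The article states no bias figure, so there is none to reproduce. The check has two parts.

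**1. What each planned sensitivity analysis can address**

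- UTI control (Section 2.6.6, Table 1): confounding by causes that UTI shares with the outcomes. Healthcare seeking, health status, age, sex and immunosuppressive treatment are plausible.
- Deleting a tenth of vaccination dates (Section 2.5.2): exposure misclassification.
- Vaccination-plan indicator (Table 2): timing of medication around vaccination.
- Weighted Kaplan-Meier with entropy balancing (Section 2.6.2): the modelling of the recorded confounders.
- Intention-to-treat (Section 2.6.3): non-adherence.
- Outcome-date analyses (Section 2.5.3, details in the supplement): dating of outpatient diagnoses.

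None of these addresses under-recorded immunity or cautiousness.

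**2. Size, with assumed inputs**

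For a binary unrecorded factor with prevalence p1 in vaccinated persons and p0 in controls, and relative risk r on the outcome:

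B = [1 + p1(r − 1)] / [1 + p0(r − 1)], and observed VE = 1 − (1 − true VE) × B.

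True VE is set at 40%, so observed VE = 1 − 0.60 × B. All p and r values are assumptions.

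| Unrecorded immunity (p1, p0, r) | B | Observed VE | UTI RR (r = 1) |
|---|---|---|---|
| 0.30, 0.20, 0.7 | 0.91/0.94 = 0.968 | 41.9% | 1.00 |
| 0.50, 0.20, 0.3 | 0.65/0.86 = 0.756 | 54.7% | 1.00 |
| 0.20, 0.40, 0.7 | 0.94/0.88 = 1.068 | 35.9% | 1.00 |
| 0.20, 0.40, 0.3 | 0.86/0.72 = 1.194 | 28.3% | 1.00 |

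The bias can go either way. The UTI relative risk stays at 1.00 because r = 1 makes B equal to 1 whatever p1 and p0 are.

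*Cautiousness.* Here r is the effect of low caution on influenza, and low caution is also allowed to raise UTI risk by 10%.

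| Low caution (p1, p0, r) | B, influenza | Observed VE | UTI RR if r = 1.1 |
|---|---|---|---|
| 0.55, 0.50, 1.5 | 1.275/1.25 = 1.020 | 38.8% | 1.005 |
| 0.60, 0.40, 2.0 | 1.60/1.40 = 1.143 | 31.4% | 1.06/1.04 = 1.019 |
| 0.40, 0.50, 2.0 | 1.40/1.50 = 0.933 | 44.0% | 1.04/1.05 = 0.990 |

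So a signal is possible, but it is much smaller than the bias. With an assumed 10,000 UTI events and 1:1 allocation, power to detect a hazard ratio of 1.02 is about 17%.

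*Simulation.* 2,000,000 persons; true influenza RR 0.60; immunity in 30% of persons with RR 0.4 on influenza, recorded with 20% to 40% sensitivity; adjustment for healthcare seeking and recorded immunity.

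- Influenza RR 0.555 (95% CI 0.546 to 0.565): biased.
- UTI RR 1.010 (0.997 to 1.022): compatible with no effect.
- UTI RR with healthcare seeking left out of the model: 1.075 (1.061 to 1.088).

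The control responds to the confounder it shares with influenza and not to pathogen-specific immunity.

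*Contrast.* Suppose true VE is 40% in both groups and the bias acts only in the diseased group. The true VE ratio of 1.00 would then be observed between 0.283/0.40 = 0.71 and 0.547/0.40 = 1.37. With the same B in both groups it would stay at 1.00.

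**The case against.** The case for leaving the text alone has several parts.

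- **The article is already cautious.** Section 2.6.5 concedes that exchangeability may fail and asks for careful interpretation, and the Discussion promises only an attempt at quantification. This stands. A reader might infer that a null UTI result will be presented as proof of little residual confounding, but no passage says so.
- **The definition of a negative control is an ideal.** A control that shares some causes is partial and not failed, and Section 2.6.6 supports UTI by its use in earlier vaccine studies. This stands too. A reader might infer that UTI is a bad control, or that it tests only healthcare seeking and frailty. Treatment, age and sex are plausibly shared as well.
- **Cautiousness is dealt with separately.** Section 2.5.4 cites a study suggesting only a slight link with vaccination and expects little bias. The sentence pointing to Section 2.6.6 concerns immunity; the link to cautiousness comes from the Discussion. A reader might infer that UTI misses cautiousness entirely. The documents do not support that, since Table 2 includes general precautionary behaviour and an indirect association is possible. The expectation of little bias is nevertheless a separate argument and does not make UTI able to measure it.
- **Prior-year influenza vaccination is recorded and adjusted for.** This narrows the immunity gap in the influenza trials mainly to unattended infections. It does not close it.
- **Section 2.5.2 rules out standard quantitative bias analysis as too complex.** That statement concerns vaccination misclassification. A bias-factor table or an E-value needs only the final estimates.

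The explicit cross-reference for immunity remains unanswered. It is not a matter of an article condensing a fuller plan, because the section it points to is shown in the article.

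**Conclusion.** The point holds in a limited form. Section 2.6.6 cannot quantify bias from under-recorded influenza or zoster immunity, although Section 2.5.4 says it will. For cautiousness it can give at most a weak, indirect signal that would understate the bias. The UTI control is still worth running for the confounding it shares with the outcomes.

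The conclusion on immunity is one of logic and rests on a single premise: the immunity defined in Table 2 does not affect UTI risk. The DAG figure is not available here, but its caption lists only the two main outcomes and nothing in the text contradicts the premise. The observed VE range of about 28% to 55% illustrates what could go unseen. It rests wholly on assumed prevalences and effects and does not predict the bias in this study.

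**What to change.** 1. In Section 2.6.6, limit the stated purpose to residual confounding by causes that UTI shares with the study outcomes, for example healthcare seeking, health status and immunosuppressive treatment.
2. In Section 2.5.4, remove or correct the reference to Section 2.6.6 for immunity.
3. State in advance that a null UTI result does not exclude bias from immunity or cautiousness.
4. Add a bias-factor table (prevalence difference by hazard ratio, over stated ranges and in both directions) or E-values, for each VE and for the VE contrast. For the contrast, apply the factors to each disease group's relative risk and recompute the ratio.

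Two further controls are optional and limited. An early-window analysis of the study outcome makes sense only where event dates are exact, because outpatient diagnoses may be dated only to an interval of up to 91 days (Section 2.5.3). A non-influenza respiratory control would address contact behaviour in the influenza trials, but not immunity, and would do nothing for zoster. It would also need its own outcome definition and dating rules.

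The cost is a few sentences and one table that rests on assumed parameters, together with a more modest claim for the negative control. No new data are needed.

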### 2.6 Data analysis plan

The main analyses will be conducted using a combination of time-dependent matching (55, 56) and a multivariable Cox proportional hazards regression model (57). Similar approaches have been used to study the effectiveness of COVID-19 vaccines (28) and are generally quite popular when analyzing the effect of a time-dependent variable on a time-to-event outcome (58). Below we first describe how the matching will be performed. Afterwards a detailed explanation of the planned analysis of the matched data is given, as well as a description of how possible intercurrent events are handled, a discussion of the required assumptions and the planned sensitivity analysis.

#### 2.6.1 Matching method

Due to the different target trials per vaccine of interest, the planned matching and analysis strategy also differs slightly. To analyze the effectiveness of the herpes zoster vaccine, a single matching process will be used. For the influenza vaccine effectiveness trials we will use the same procedure, with the only difference being that it will be performed separately for each influenza season. The matching will be carried out as follows.

For the previously defined start date of the respective trial, the eligibility of all individuals contained in the BARMER database will be determined using the above mentioned inclusion criteria. Eligibility will be checked using only the information available at that time. Every individual who was vaccinated with the vaccine of interest on this date is subsequently included in the dataset, in the treatment group. For every individual included in this way, we then include *k* further individuals who fulfill the inclusion criteria, but have not been vaccinated yet, in the control group. These controls will be matched exactly by age in years, gender, place of residence and disease group. If more than *k* potential controls are identified for a case, *k* controls will be picked at random from these. We will try to include 2 controls per case first (*k* = 2), but will lower this number to 1 if the number of available matches is insufficient. The date of inclusion equals “time zero” (27) for all individuals. Information about all relevant confounders is recorded as available on this date, corresponding to baseline information. This procedure is repeated on all subsequent days, until the emulated trial is over.

Controls will be matched without replacement, meaning that individual *i* who was used as a control at one point in time *t* cannot serve as control more than once at the same point in time and can also not be used as control again at later points in time. However, people who have been used as controls will still be included in the trial later, if they get vaccinated. They will then be included in the treatment group, again with the vaccination date corresponding to the trial inclusion date. Information about the different defined outcomes are extracted from the BARMER data for each individual. This matching procedure results in datasets that are similar to what we would obtain if we actually had performed the respective target trials. The main advantage of this method is that it directly matches patients by inclusion-date, giving us a clearly defined “time zero” (27). Because controls are choosen to be similar to vaccinated individuals, this matching methods targets the *average treatment effect on the treated* (ATT) (56).

If no suitable control can be identified for a vaccinated individual at the time of vaccination, the individual is not included in the analysis. Because of the large amount of data, the long follow-up time and the fact that only a relatively small proportion of individuals gets vaccinated, we believe that only a small proportion of individuals will be excluded. If the proportion of vaccinated individuals with no matched controls exceeds 10%, we will adjust the choice of matching variables to lower this proportion. This will be done by either widening the age groups or not matching by sex. In theory, methods other than exact matching, such as generalized full matching (59) would offer a viable alternative in such cases. It would also allow matching on more confounders, which would be preferable. We unfortunately cannot use such methods, due to the high computational complexity of our approach and the limited available technical infrastructure.

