A detailed list of all International Statistical Classification of Diseases and Related Health Problems (ICD)-10 Codes used to assess the inclusion criteria is given in the online supplement. We require two years of previous enrolment in the BARMER because we would otherwise be unable to obtain information on all relevant confounders as described in Section 2.5.4. In these 2 years of enrolment, small interruptions are allowed (up to 5% of the total time), as a compromise between the potential for misclassification that arises, because no information is recorded when a person is not insured at BARMER, and the available sample size. The studies are further constrained to contain only biological males and females due to small amounts and inconsistent coding of the “diverse” category in the BARMER data. People with cancer, previous organ transplantations and other autoimmune diseases are excluded due to the effect these conditions and/or their treatment have on the immune system. There are no other exclusion criteria in this study. Special populations, such as pregnant women and people with other chronic or life-threatening diseases are also eligible to be included in the study.

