#### 2.5.2 Treatments

The “treatments” in this study are the two different types of vaccines of interest. We will not differentiate between different subtypes of vaccines in the influenza vaccine effectiveness trials. Any vaccine against influenza will be considered an “influenza vaccine”, regardless of its' underlying mechanism and irrespective of which company created the vaccine. In the herpes zoster trial we will only consider the inactivated recombinant zoster vaccine (Shringrix^®^) (41). In Germany, vaccinations are usually provided by physicians in primary care. Physicians receive a reimbursement for each vaccination from the statutory health insurance of the individual being vaccinated. To this end, a standardized reimbursement code [German: Gebührenordnungsposition (GOP)] is used and transferred to the insurance as part of a reimbursement claim. We will use these codes to identify vaccinations in our study population, using both codes applying uniformly for all regions in Germany and codes only used for specific regions and time periods. The reimbursement codes used are listed in the online supplement.

There is, however, one special case that needs to be mentioned. Whenever individuals get vaccinated through a company physician (in German: Betriebsärzte), the reimbursement code is not transferred to the insurance company of the individual. The reimbursement is instead taken care of by the companies themselves. Additionally, a few pharmacies and hospitals also vaccinate individuals without sending reimbursement codes to the insurance company (42). Because these vaccinations never show up in the individuals data of the health insurance, the vaccination status of these individuals will be misclassified in the analysis. We expect this issue to have a minor impact, because the majority of vaccinations are performed by primary care physicians in Germany. There is currently no official data available to quantify the proportion of vaccinations performed in these different settings. Due to the complex nature of the proposed analysis strategy, as described in Section 2.6, it is also not possible to apply standard methods of quantitative bias analysis to quantify the effects of this potential bias (43). To still get a rough estimate of the potential impact of this misclassification, we will repeat the main analysis after removing 10% of all vaccination dates from the available data in a sensitivity analysis.

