#### 2.5.3 Outcomes

Different outcomes will be used for each of the considered vaccine effectiveness trials. For the emulation of the proposed target trials, the date on which the respective outcomes occurred is required. Our aim is therefore to identify this date of occurrence given the available insurance claims data. In the German system, ICD-10 codes that were used in the inpatient setting are directly associated with an exact date. Outpatient ICD-10 diagnosis, however, are only associated with a time interval which may be up to 91 days (one quarter) long, depending on the patient. In some cases, the corresponding date of the diagnosis must therefore be identified using associated treatments or doctors certificates on the incapacity to work, for which exact dates are available. The concrete strategy used to identify the dates for outpatient diagnosis of each defined outcome and associated sensitivity analyses are described in the online supplement.

The outcome for the herpes zoster vaccine effectiveness analysis is a *medically attended herpes zoster infection*. This outcome will be identified from the available data through the use of ICD-10 code **B02** (inpatient or outpatient diagnosis), in conjunction with a prescription for an antiviral drug (acyclovir, valacyclovir, famciclovir, or brivudin). This is similar to the definition proposed by Zerbo et al. (44), which was estimated to have a positive predictive value of 96.7% by the same authors. Other studies additionally employed information about positive laboratory tests (45), which is not possible in this study due to a lack of available data.

For the influenza vaccine trials we will use *medically attended influenza* as the primary outcome, as recommenced in the literature (30, 46). We define a medically attended influenza as an influenza infection that results in any type of formal contact between the patient and a health care professional. In particular, we define a medically attended influenza infection as having occurred when either one of the ICD-Codes **J09**, **J10**, or **J11** has been used as a secured outpatient diagnosis or in an inpatient main or secondary diagnosis. The medically attended influenza is considered to be *severe* if it is associated with a hospital admission due to pneumonia or death. We will use the severe medically attended influenza as a secondary outcome.

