**Health status**	
The general health status of an individual. This includes both physical and psychological wellbeing.	Two indicators will be used as proxies for this variable. We will consider: (1) A modified version of the Charlson comorbidity index (81) that does not include the main diseases of interest in this study, calculated using ICD codes from the last year. (2) The number of inpatient hospital stays in the last 2 years. (3) The current official level of care.

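### Hospital inpatients can be drawn as controls at time zero although recorded vaccinees are almost never inpatients, which leaves residual confounding by acute illness, probably small and probably upward for influenza

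*Protocol article*

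**What the plan says.** All references are to the protocol article.

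- **Control rule (section 2.6.1).** On each day, everyone vaccinated that day enters the treated arm. For each of them the plan adds *k* "further individuals who fulfill the inclusion criteria, but have not been vaccinated yet, in the control group", picked at random if more than *k* qualify. On the matching variables it says: "These controls will be matched exactly by age in years, gender, place of residence and disease group".
- **Eligibility (section 2.3 and Table 1).** The criteria concern enrolment, age, sex, transplantation, cancer, other autoimmune disease and prior vaccination. Section 2.3 then states: "There are no other exclusion criteria in this study". It adds that "people with other chronic or life-threatening diseases are also eligible to be included in the study".
- **Source of vaccination dates (section 2.5.2).** Vaccinations are identified from reimbursement codes, and "vaccinations are usually provided by physicians in primary care". The section also notes that "a few pharmacies and hospitals also vaccinate individuals without sending reimbursement codes to the insurance company".
- **Nearest covariates (Table 2).** Under health status the plan lists a comorbidity index over the last year, the current level of care, and "The number of inpatient hospital stays in the last 2 years". Under healthcare-seeking behaviour it lists physician visits, pneumococcal vaccination and a preventive check-up.
- **Outcome (section 2.5.3).** Influenza counts if one of the listed codes "has been used as a secured outpatient diagnosis or in an inpatient main or secondary diagnosis". Zoster needs its diagnosis code together with an antiviral prescription.
- **Follow-up and estimand.** Table 1 starts follow-up at assignment, with no lag. Section 2.6.1 says the matching targets the average effect in the treated.

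**The concern.** A recorded vaccinee was, almost always, outside hospital and well enough to be vaccinated on the day of inclusion. A control on the same day need only meet the eligibility list and have no recorded vaccination. The two arms therefore differ at time zero in whether a person can be acutely ill in hospital, and that difference is created by the selection rule.

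If inpatients have a higher short-term risk of a coded influenza infection, the excess events fall in the control arm and VE is overstated. Because VE is reported as a function of time (section 2.6.2), the early part of the curve is the most exposed. If the inpatient share also differs between people with and without MS, IBD or CIRD, the error could reach the main contrast, which is the ratio of their VEs.

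**Working it through.** **Step 1. Does any planned step close the gap?**

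| Planned step | Does it mark a hospital stay in progress at time zero? |
|---|---|
| Eligibility list (2.3, Table 1) | No, and the list is closed |
| Exact matching (2.6.1) | No: age, sex, residence, disease group |
| Count of stays over 2 years (Table 2) | No: two people with the same count can differ in whether they are in hospital today |
| Comorbidity index, level of care, visit counts (Table 2) | No: they are related to it but do not identify it |
| Start of follow-up (Table 1) | No lag, so the first days count |
| Urinary tract infection as negative control (2.6.6) | Can reveal such a bias but does not remove it |

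The gap follows from the text alone and needs no assumed figure.

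**Step 2. How large could it be?** The article states no figure on this point, so there is none to reproduce. Let *p* be the share of controls in hospital at time zero and *h* their outcome risk relative to other controls, with no inpatients among vaccinees. The control risk is multiplied by 1 + *p*(*h* − 1), so

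RR(observed) = RR(true) / [1 + *p*(*h* − 1)], and VE(observed) = 1 − RR(observed).

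Assumed inputs, none of them in the document: *p* = 0.5% to 1%, *h* = 3 to 10, true VE = 40% (RR 0.60). The ratio *h* is held over the whole follow-up and taken before covariate adjustment.

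| *p* | *h* | 1 + *p*(*h* − 1) | RR observed | VE observed |
|---|---|---|---|---|
| 0.5% | 3 | 1 + 0.005 × 2 = 1.01 | 0.60/1.01 = 0.594 | 40.6% |
| 0.5% | 5 | 1 + 0.005 × 4 = 1.02 | 0.60/1.02 = 0.588 | 41.2% |
| 0.5% | 10 | 1 + 0.005 × 9 = 1.045 | 0.60/1.045 = 0.574 | 42.6% |
| 1% | 3 | 1 + 0.01 × 2 = 1.02 | 0.60/1.02 = 0.588 | 41.2% |
| 1% | 10 | 1 + 0.01 × 9 = 1.09 | 0.60/1.09 = 0.550 | 45.0% |

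With a true VE of 0, the two end rows read 1 − 1/1.01 = 1.0% and 1 − 1/1.09 = 8.3%.

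**Step 3. Sensitivity to the assumptions.**

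- *Direction.* If adjusted inpatient risk were lower than that of other controls (*h* = 0.5), a true VE of 40% would read 39.85% (*p* = 0.5%: 0.60/0.9975) or 39.7% (*p* = 1%: 0.60/0.995).
- *Early follow-up.* A high *h* is more credible over the first days than over a season. With an assumed *h* = 50 and a true VE of 0, the early reading is 1 − 1/1.245 = 19.7% (*p* = 0.5%) or 1 − 1/1.49 = 32.9% (*p* = 1%).
- *Ratio of VEs.* Suppose the true VE is 40% in both groups, with 0.5% inpatients in the non-diseased and 1% in the diseased. A true ratio of 1 then reads 41.18/40.59 = 1.01 (*h* = 3) to 44.95/42.58 = 1.06 (*h* = 10).
- *Opposing bias.* If a share *m* of controls is vaccinated without record, RR(observed) = RR(true)/(1 − *m* × VE). For *m* = 1%, 5% and 10%, a true VE of 40% reads 39.8%, 38.8% and 37.5%.

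**Step 4. After the fix.** With current inpatients barred from both arms, *p* = 0 and this term vanishes.

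**The case against.** The strongest reply is that the effect is small and already partly covered. The Cox model adjusts for stays over 2 years, comorbidity, level of care and visits, which absorbs some of the excess risk. Being in hospital on one day need not raise risk until 31 May, still less over the zoster trial's roughly three years. The article admits residual confounding and plans a negative control outcome. Unrecorded vaccination among controls pulls VE down. All of this stands as a limit on size. None of it removes the asymmetry at time zero, and an opposing bias is no reason to keep this one.

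Four stronger readings are tempting, and the documents do not support them.

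- *VE is inflated, as a fact.* Direction and size depend on an inpatient share and an inpatient risk that the article does not give. Upward is probable for influenza. For zoster it is open, because the outcome also needs an antiviral prescription and the article does not say whether drugs given in hospital count.
- *A positivity failure.* The target is the effect in the treated. That requires that people like the vaccinees could have gone unvaccinated; it does not require every control to have a vaccinated counterpart. The accurate label is residual confounding by acute illness.
- *Severe influenza is hit hardest.* Under section 2.5.3 pneumonia or death alone is not an event; it must accompany a medically attended influenza. Someone already in hospital for another reason does not gain an admission due to pneumonia by catching influenza there, and section 2.6.3 censors at death. A larger bias for this outcome is not established.
- *The diseased versus non-diseased contrast is biased.* Controls are matched within disease group, so this needs unequal inpatient shares between the groups, which the article does not report.

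Nor does section 2.5.2 say that no hospital vaccination is ever recorded; it speaks of a few hospitals. Recorded vaccinees are almost never inpatients, which is weaker than never.

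**Conclusion.** The point holds as a gap in the control rule. Read together, sections 2.3, 2.5.2 and 2.6.1 allow a current inpatient to be a control while recorded vaccinees are almost never inpatients, and no matching variable or named covariate marks the difference. For influenza the result is probably an upward bias in VE, concentrated early in follow-up. For zoster the direction is uncertain. Any effect on the ratio of VEs depends on figures the article does not give.

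The size is unknown and probably small. Under the assumed inputs the shift for a true VE of 40% runs from 0.6 to 5.0 percentage points. The upper end needs the larger inpatient share and the larger risk ratio together, sustained over all of follow-up and untouched by covariate adjustment. The case for acting is that the asymmetry is avoidable at low cost.

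**What to change.** Add one criterion, applied to both arms, to the list in section 2.3 and to Table 1: not a hospital inpatient on the date of inclusion. Section 2.5.3 says inpatient diagnoses carry exact dates. The rule assumes that admission and discharge dates can be taken from the same records.

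Optional: a sensitivity analysis that also excludes people discharged shortly before inclusion, for example within 14 days. That window is a choice and does not follow from the article.

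The cost is one filter on data already held. It adds no matching variable, so the computing limits described in section 2.6.1 are not affected. A small share of potential controls and almost no vaccinees are lost. The estimand becomes limited to people not in hospital at inclusion, which already describes nearly every recorded vaccinee.
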